### Ethics and dissemination

2.12

The present study has been approved by the Regional Ethical Review Board in Uppsala, Sweden (Dnr 2016/230/2) and registered in ClinicalTrials.gov (NCT04586517), registered on 14 October, 2020. The study will be performed in accordance with the Declaration of Helsinki and written informed consent according to GDPR guidelines will be obtained from the participants. Collections of biological material as blood and tissue samples will be stored according to the Regional Biobank in Uppsala. Results will be disseminated through presentations at scientific meetings, publications in peer-reviewed journals, social media, and patient organizations. A data sharing plan has been established, where de-identified individual data on participant characteristics and main study outcomes will be made available on reasonable request once the results are published.

## Discussion

3

The present study aims to investigate the effects of a heavy-load resistance-training program on skeletal muscle cellular outcomes in women diagnosed with breast cancer undergoing chemotherapy. The results are expected to provide insights about the mechanism involved in side effects of chemotherapy on skeletal muscle. Such knowledge can be used to design effective physical exercise programs to support individuals with breast cancer during and following chemotherapy and possibly reduce long-lasting side effects such as impairments in physical function, fatigue, and risk for comorbidities.

To our knowledge, this will be the first randomized controlled study evaluating heavy-load RT during (neo-)adjuvant chemotherapy treatment in breast cancer patients to explore its effects on muscle cellular outcomes in a relatively larger study population in comparison to previous studies.^[13,33,34]^ Although the primary outcome of this present study is muscle fiber CSA, we are also including a wide range of biological measurements, including specific proteins involved in skeletal muscle hypertrophy/degradation and regulators of muscle fiber function. These analyses will provide further insight into the underlying mechanism through which chemotherapy affects muscle tissue and how RT could be used as a therapeutic measure to counteract immediate and long-term treatment side effects. As exercise has been suggested to have an antitumor effect^[26]^ regular exercise could have a positive effect on the recurrence rate. In this study, we will investigate changes in myokines with potential antitumor effect in both muscle tissue and blood and these results will give valuable insight to exercise-induced antitumor mechanisms. However, the possible effect on cancer recurrence rate has to be further explored in future longitudinal studies as our study will only include follow-up measures at 6 months post end of treatment. Importantly, the feasibility of the training program has been confirmed by a previous study (Phys-Can study)^[29]^) in which ∼75% of participants completed the 6-month training program with an exercise adherence of approximately 67%.

In summary, previous research underlines the potential of physical exercise during cancer treatment on improving outcomes such as physical function, mental health, fatigue, and quality of life in women with breast cancer.^[35–37]^ However, research on the specific cellular effects of RT during chemotherapy is scarce. This study will provide important knowledge regarding the effects of heavy-load RT on skeletal muscle cellular outcomes. In addition, increased knowledge regarding the effects of RT on a selection of antitumor myokines as well as muscle strength and cardiorespiratory fitness may be provided.

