## Introduction

1

The increasing survival rates of women diagnosed with breast cancer requires an increased focus on measures to counteract persistent adverse effects of treatment. Neo-adjuvant treatment aims to decrease tumor burden before surgery and adjuvant treatment to inhibit proliferation in eventual remaining cancer cells after surgery. A common (neo-)adjuvant treatment for women with breast cancer is combined chemotherapy with anthracyclines and taxanes, given in 3 cycles of each chemotherapy type with a recovery period after each cycle.^[1]^ Anthracyclines have a cardiotoxic effect^[2,3]^ and previous observational studies have shown approximately 10% decrease in maximal oxygen uptake (VO_2max_) during chemotherapy.^[4]^ VO_2max_ is determined by both central- (e.g., cardiac function) and peripheral factors (e.g., skeletal muscle function) and reductions in VO_2max_ are common in patients with breast cancer without any signs of impaired cardiac function.^[5]^ This suggests that there may be changes in peripheral factors affecting oxygen transport, however, this must be further elucidated. Direct negative effects of chemotherapy on skeletal muscles are documented in animal studies, where anthracyclines impair force-generating capacity and mitochondrial function in skeletal muscles.^[6–9]^ These findings are supported by analysis on muscle biopsies from patients with prostate cancer,^[10]^ testicular cancer,^[11]^ and in 2 small-scale studies on patients with breast cancer undergoing chemotherapy.^[12,13]^ The effects of treatment with taxanes on skeletal muscle are less studied. However, muscle and joint pain, referred to as “taxane acute pain syndrome”^[14]^ is commonly reported and occurs about 24 to 48 hours after treatment and lasts for about 5 to 7 days.^[15]^ Altogether, previous studies confirm the deleterious effects of chemotherapy on muscle size, mitochondrial structures, and muscle function. An alternative reason for these muscle changes could be reduced levels of physical activity, which is common in patients with cancer.^[16]^ Epidemiological studies have found that patients receiving chemotherapy decrease their level of physical activity during treatment, and this reduction may still be present after the end of the treatment period.^[17,18]^ Regardless of cause, loss of skeletal muscle mass has been associated with reduced physical functioning and increased toxicity, that is poor tolerance to chemotherapy, and consequently worse prognosis.^[19,20]^

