### Study design

2.1

This study is a two-armed randomized controlled trial with follow-up at 6 months (Fig. 1). Data will be collected before the first cycle of chemotherapy (T0), after chemotherapy (T1), and 6 months later (T2). The primary outcome for this study is muscle fiber size. Secondary outcomes are: regulators of muscle fiber size and function, indicators of cellular stress and mitochondrial function, myokines with potential antitumor effects, muscle strength, and cardiorespiratory fitness. All outcomes are listed in Table 1.

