	Adverse events occurring during muscle biopsy sampling	Reported by technicians	x	x	x

4EBP1 = Eukaryotic translation initiation factor 4E-binding protein 1, BIA = Bioelectrical impedance analysis, CK-MB = creatine kinase-myocardial band, Cox 4 = cytochrome c oxidase subunit 4, CRP = C-reactive protein, CS = citrate synthase, CSA = cross-sectional area, eIF4A = eukaryotic initiation factor-4A, EORTC QLQ-C30 = European Organization for the Research and Treatment of Cancer Quality of Life Questionnaire Core 30, HAD = 3-hydroxyacyl-CoA-dehydrogenase, Hsp27, 60 and 70 = heat shock protein 27, 60 and 70, IFN-γ = Interferon gamma, IL-6, -8, -10, -15, -1β = Interleukin- 6, -8, -10, -15 and 1beta, MFI = Multidimensional fatigue inventory, mTOR = mechanistic target of rapamycin, p62 = ubiquitin-binding protein p62, P70s6k = ribosomal protein S6 kinase, QLQ-BR25 = The European organization for research and treatment of cancer quality of life questionnaire, SC = satellite cell, SPARC = secreted protein acidic and rich in cysteine (Osteonectin), T0 = before start of chemotherapy and training intervention, T1 = after chemotherapy and training intervention, T2 = 6-month follow-up, TNF-α = tumor necrosis factor alpha, TNFR1 = tumor necrosis factor receptor 1, TWEAK = TNF-related weak inducer of apoptosis, VO^2^max = maximal oxygen uptake.

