### Participant recruitment and eligibility criteria

2.2

Women recently diagnosed with breast cancer will be recruited from Uppsala University Hospital.

Eligibility criteria are:

1.women diagnosed with stage I-III breast cancer,2.>18 years old,3.literate in Swedish,4.scheduled to undergo (neo-)adjuvant chemotherapy with a combination of taxanes and anthracyclines or only 1 of these treatments.

Exclusion criteria are:

1.unable to perform basic activities of daily living,2.cognitive disorders or severe emotional instability,3.other disabling comorbidities that might hamper physical training (e.g., severe heart failure, chronic obstructive pulmonary disease, orthopedic conditions, and neurological disorders).

Eligibility will be assessed by treating surgeons or medical oncologists, and all eligible women will receive written information. Women who meet the inclusion criteria will be provided with further information about the study and written informed consent will be obtained by research staff. Based on the experience gained from on-going studies and previous relevant studies within the research group, an inclusion rate of 35% to 40% can be expected. The study was initiated in December 2018 and with the expected inclusion rate; the last participants will complete the intervention during the second half of 2021.

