### Randomization

2.4

After completion of baseline measurements, participants will be randomized by research staff in a 1:1 ratio to either the *intervention group* (supervised heavy-load RT during chemotherapy treatment) or to the *control group* (activity as usual during chemotherapy treatment), stratified on treatment (neo-adjuvant or adjuvant treatment). Sealed envelopes will be used to conceal the group allocation.

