### Statistical analyses

2.11

Data will be analyzed according to the intention-to-treat principle. Analyses will include standard descriptive statistics, *t* tests, correlation, regression and two-way repeated-measures ANOVA or the comparable nonparametric test as necessary to examine differences between and within groups, at T0, T1, and T2. In addition, a per-protocol analysis, that is, adherence to the protocol, will be conducted. Should imbalances in important variables be detected, sensitivity analyses will also be added including these as covariates in the model. All data will be cleaned and quality-checked before analysis.

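### Within-group change over T0, T1 and T2 mixes two surgical courses, and the named repeated-measures analysis leaves out the stratification factor that separates them

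*Protocol article*

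**What the plan says.** Section 2.1 places the last two visits "after chemotherapy (T1), and 6 months later (T2". The footnote to Table 1 agrees: "T1 = after chemotherapy and training intervention, T2 = 6-month follow-up". The Discussion, when explaining why recurrence cannot be studied, says that "our study will only include follow-up measures at 6 months post end of treatment".

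The Introduction fixes the order of surgery and chemotherapy: "Neo-adjuvant treatment aims to decrease tumor burden before surgery and adjuvant treatment to inhibit proliferation in eventual remaining cancer cells after surgery". Both settings are eligible, since section 2.2 admits women "scheduled to undergo (neo-)adjuvant chemotherapy with a combination of taxanes and anthracyclines or only 1 of these treatments". Section 2.4 stratifies the 1:1 randomisation on setting (neo-adjuvant or adjuvant).

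Section 2.11 lists t tests, correlation, regression and a two-way repeated-measures ANOVA, or nonparametric counterparts, "to examine differences between and within groups, at T0, T1, and T2". Other variables enter as covariates only in sensitivity analyses, and only if imbalance is detected. Treatment setting is not mentioned there.

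**The concern.** The three visits do not mark the same stages of care in the two strata. For an adjuvant woman, T0 to T1 is chemotherapy after a recent operation, and T1 to T2 has no primary breast operation still to come. For a neo-adjuvant woman, T0 to T1 is chemotherapy without prior surgery, and T1 to T2 is expected to contain the operation.

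This matters most for analyses that randomisation does not protect. Hypothesis 1 states that chemotherapy itself reduces fiber size, strength and fitness. Every participant receives chemotherapy, so only change over time within a group can address it. A within-group T1-T2 change may also be read as recovery from chemotherapy when part of it reflects surgery. Chest-press strength and physical activity are outcomes for which surgery is a plausible influence.

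**Working it through.** There is no planned figure to reproduce on this point. The check sets the timing statements side by side and then illustrates the size.

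**1. What each interval contains**

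| Interval | Adjuvant | Neo-adjuvant |
|---|---|---|
| Before T0 | Surgery | No surgery yet |
| T0 to T1 | Chemotherapy, after surgery | Chemotherapy, before surgery |
| T1 to T2 | No primary surgery to come | Surgery expected (inferred) |

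The order comes from the Introduction and the visit anchors from section 2.1 and the Table 1 footnote. Surgery falling between T1 and T2 is an inference: the article gives no surgery date relative to either visit.

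**2. Whether the stated analysis separates the courses**

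A two-way repeated-measures ANOVA between and within groups reads as arm by visit. Setting could otherwise enter through the covariate rule, but that rule is triggered by imbalance, and a stratification factor is unlikely to be imbalanced. A constant setting effect would not be enough either. It adds the same amount at each visit and cancels from every change score, whereas here the change between visits differs. An interaction of setting with visit is needed.

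**3. Formulas**

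Let f be the neo-adjuvant share and s the effect of surgery at T2, equal in both arms.

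- Shift in pooled within-arm change: f × s.
- Shift in the between-arm difference: f × s − f × s = 0 when f is the same in both arms.
- Variance added if setting by visit is not modelled: f(1 − f)s².

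**4. Illustration for fiber area**

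Inputs from section 2.3: difference 898 μm², SD 840 μm², 16 per arm. Assumed, because the article gives neither: f from 20% to 50% and s from 200 to 600 μm² (a reduction). Also assumed: a two-sided 5% t test.

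- Within-arm shift: 0.2 × 200 = 40 μm², up to 0.5 × 600 = 300 μm². Against 898 μm² this is about 4% to 33%.
- SD: √(840² + 0.2 × 0.8 × 200²) = √712,000 ≈ 844, up to √(840² + 0.5 × 0.5 × 600²) = √795,600 ≈ 892 μm².
- Power at 16 per arm: 83% at SD 840, and 79% to 83% over the range.

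The 83% is below the 95% that section 2.3 gives for 16 per arm. That is a separate matter and does not affect this point.

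**5. Cost in degrees of freedom**

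Setting uses 1 and setting by visit (three visits) uses 2, so 3 in total. With 50 complete participants in two arms, between-participant error falls from 48 to 47 and within-participant error from 96 to 94.

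**The case against.** **The Discussion phrase is not an error.** A reader might infer that the article contradicts itself on T2. It does not. The phrase is an aside about recurrence, the Methods define T2 consistently, and the article often uses the word treatment for chemotherapy. This objection stands; the wording is loose.

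**Randomisation protects the trial.** A reader might infer that the T2 comparison of arms is biased. It is not. Stratified 1:1 allocation balances setting, and a surgery effect common to both arms cancels. Persistence of the training effect can be read from that comparison, so T1-T2 change is not the only evidence on it. The T0-T1 comparison of arms is unaffected by surgery after T1. All of this stands, but it does not extend to within-group change.

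**Pooling is inferred from silence.** The article is condensed, and an analysis plan that is not shown may contain a setting term. This stands in part. The article is not wholly silent, however: it names an analysis and a route for covariates, and that route is unlikely to bring setting in.

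**The size is assumed.** One can choose opposite changes in the two strata so that the pooled T1-T2 change reverses sign with the mix. No figure in the article supports such a scenario. The biopsy is from the vastus lateralis, and nothing in the article suggests that breast surgery alters it. This stands, and the figures above are illustrations only.

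**Strata are small.** At a 20% neo-adjuvant share there are 5 such women per arm before drop-out (0.2 × 25), and at 50% about 12 or 13. This argues against requiring formal stratum-specific inference or ruling out every pooled conclusion.

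**Conclusion.** The point holds with limited scope. By the article's own definitions, the intervals between visits cover different courses in the two randomisation strata, and the stated analysis omits the factor that distinguishes them. The consequence falls on within-group change: on hypothesis 1, because adjuvant women start from a post-surgical baseline, and on any reading of T1-T2 change as recovery from chemotherapy. The effect on the randomised contrast is on precision only and is small, at most about 4 percentage points of power in the illustration.

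This rests on neo-adjuvant surgery falling between T1 and T2, which is likely but not stated, and on the named ANOVA being arm by visit without setting. The within-arm shift of 40 to 300 μm² depends wholly on the assumed share and surgery effect. It shows scale and does not predict a result.

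**What to change.** - **Section 2.11:** include treatment setting (neo-adjuvant or adjuvant) and its interaction with visit in the main longitudinal model, rather than leaving setting to the imbalance rule. Cost: about 3 degrees of freedom.
- **Section 2.10.5:** add the date of surgery to the medical-record extraction already planned. Cost: one data field.
- **Reporting:** show T1-T2 change by setting descriptively, labelled as imprecise, and interpret within-group T2 change with surgery in mind. Pooled results may still be reported.
- **Discussion (minor):** describe the follow-up as 6 months after the end of chemotherapy.

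No visit, procedure or sample size changes.
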